#### Ethical considerations

Ethical approval was granted by the National Research Ethics Service Committee London, Dulwich (Reference number: 11/LO/0220), and by the Research and Development Department at King’s College Hospital (R&D Reference number: KCH12-013). Funding was provided through King’s College London PhD funds. Informed consent will be sought from each participating parent or guardian and assent will be sought from the children themselves. Participants will be able to withdraw from the trial at any time and this will not affect access to their treatment at the hospital.

All information disclosed in the study will be kept confidential and participants will not be identifiable in any material published as part of the study in any way. All data are stored without any identifying details. At all stages of research, the data will be stored using a password-protected computer and a secure locked cabinet; and all correspondence between research team members will be conducted using secure email.

#### Participants

The target population will be children referred for extraction of decayed teeth under general anaesthesia. Families will be invited to take part in the study at their child’s attendance at the medical pre-assessment clinic prior to their general anaesthesia appointment.

The inclusion criteria are as follows: the child is four to ten years old, does not have any learning difficulties or medical conditions complicating oral health status and is scheduled for treatment of dental caries under general anaesthesia. A parent or guardian should provide consent and both parent and child should have English proficiency.

The exclusion criteria are as follows: the child is referred for treatment of other dental conditions under general anaesthesia, has learning difficulties or a medical condition affecting oral health, is accompanied by an adult that cannot give consent, or, has been participating in another study. Families where either the parent or guardian or the child do not have sufficient English proficiency to consent or understand the advice delivered will also be excluded.

#### Sample size

The primary outcome measure in this study is user satisfaction with the intervention, assessed using a visual analogue scale. This is constructed as a continuous 100 mm line, with a score at the 0 mm mark indicating complete dissatisfaction with the intervention and a score at the 100 mm indicating complete satisfaction. As far as we know, this is the first study measuring patient’s satisfaction with the use of video games for oral health education. Assuming that our population will have a standard deviation of 25 mm, which is similar to patient satisfaction measured in studies in other fields [29], and aiming to detect a difference of at least 15 mm between the groups to indicate its clinical significance, a sample of 45 participants in each group will be needed to provide 80 % power, at the 5 % significance level, to detect effects of size 0.6 and above. This number of participants is also sufficient based on our calculations using the results of the pictorial dietary quiz used in the phase-I RCT. Anticipating a 20 % dropout rate [30], we intend to recruit approximately 108 participants.

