**Methods/Design:**

A two-armed phase-II randomized controlled trial will assess a children’s oral health education video game in comparison with verbal oral health education in terms of: family satisfaction, effect on oral health knowledge, and effect on dietary and oral hygiene habits. Up to 110 four- to ten-year-old children, referred for tooth extraction under general anaesthesia due to caries, will be recruited. A sample of 45 participants in each group will be needed to provide 80 % statistical power. The primary outcome measures for this study are: (1) parent and child satisfaction with the intervention, as indicated using a visual analogue scale; (2) improvement in the child’s dietary knowledge measured by a pictorial dietary quiz; and (3) changes in the child’s diet and oral hygiene habits, measured using a children’s dietary questionnaire completed by the parent, and snacking and toothbrushing diaries completed by the child. Measures will be taken at baseline, directly after the intervention, and three months later.

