#### Outcome measures

Fig. 3 outlines the various measures completed in the phase-II RCT. The primary outcome measures are:

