**Fig. 3 Fig3:**
[figure not shown]
Outline of measure completion. GA, general anaesthesia

Parent and child satisfaction with the intervention, as indicated using the visual analogue scale.Improvement in the child’s dietary knowledge measured by the change in pictorial dietary quiz score taken at baseline, postintervention, and after 3 months.Change in child’s diet at home, measured by children’s dietary questionnaire taken at baseline and after 3 months.Return of the child’s toothbrushing diary showing their level of engagement in toothbrushing, and return of snack diary showing reported healthy snack selection.

The secondary outcome measures are:Parent and child verbal feedback on intervention in the form of qualitative data.Completion of ‘secret words’ sheet by children in intervention group, indicating use of game DVD at home.Attendance rates for review appointment after three months.

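### The article sizes the trial on one primary outcome but lists three or four as primary and tests six comparisons from that list, so the stated 5% level and 80% power have no single result to attach to

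*Protocol article*

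**What the plan says.** The protocol article identifies the primary outcome in several places, and they differ.

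- **Sample size:** one outcome. "The primary outcome measure in this study is user satisfaction with the intervention, assessed using a visual analogue scale". The assumptions are an SD of 25 mm and a difference of 15 mm, giving 45 per group for 80% power at the 5% level. A further sentence says the number is also enough for the pictorial dietary quiz, citing phase-I results but showing no inputs. The recruitment target is about 108.
- **Abstract, Methods/Design:** several outcomes, in three groups. The list opens "The primary outcome measures for this study are: (1) parent and child satisfaction with the intervention" and goes on to dietary knowledge and to diet and oral hygiene habits.
- **Outcome measures:** several outcomes, in four items, introduced by "The primary outcome measures are". The items are:
  1. "Parent and child satisfaction with the intervention, as indicated using the visual analogue scale".
  2. The "change in pictorial dietary quiz score taken at baseline, postintervention, and after 3 months".
  3. Change in the child's diet, "measured by children’s dietary questionnaire taken at baseline and after 3 months".
  4. "Return of the child’s toothbrushing diary showing their level of engagement in toothbrushing, and return of snack diary showing reported healthy snack selection".
- **Primary aim:** satisfaction is aim (i). Knowledge and dietary and oral hygiene practices form aim (ii). Both are called primary.
- **Statistical analysis:** t tests for the parent and child satisfaction scores, the dietary questionnaire, toothbrushing and snack selection, and a regression for the quiz. No order of testing, split of the significance level or success rule appears in the article.

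**The concern.** A significance level and a power belong to a defined decision. Here the 5% and 80% are attached to one outcome, while the outcome list and the primary aims give the same standing to several others. A reader cannot tell which result decides whether the game succeeded.

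If a favourable difference on any listed outcome may be reported as a primary success, the false-positive risk exceeds the 5% used for sizing. The ambiguity also reaches the sized outcome itself: user satisfaction is scored by both the parent and the child, the two are analysed as separate scores, and the Sample size section does not say which one has 80% power.

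**Working it through.** **Step 1. Reproduce the stated sample size.** Inputs from the Sample size section: difference 15 mm, SD 25 mm, effect size 15/25 = 0.6, level 5%, power 80%. Sidedness is not stated.

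- Normal formula, two-sided: n = 2 × (1.960 + 0.842)² × 25² / 15² = 43.6, so 44 per group.
- t-based solution: 44.6, so 45 per group. Power at 45 is 80.4%.
- A one-sided 5% test needs 35 by the normal formula, so the plan's figure is a two-sided one.

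The stated 45 is correct for one comparison at two-sided 5%.

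**Step 2. Count the comparisons called primary.** The Statistical analysis section supports six: parent satisfaction, child satisfaction, dietary questionnaire, toothbrushing, snack selection and quiz. Counting one test per listed item gives four.

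**Step 3. Chance of at least one false positive** if each is tested at 5% and any one counts.

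- Independent tests, 1 − 0.95^k: k = 4 gives 1 − 0.8145 = 18.5%; k = 6 gives 1 − 0.7351 = 26.5%.
- Correlated tests: the documents give no correlation, so a range is shown. Simulated equicorrelated normal test statistics (400,000 draws) give:

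| Common correlation (assumed) | 4 tests | 6 tests |
|---|---|---|
| 0 (formula) | 18.5% | 26.5% |
| 0.3 | 17.4% | 24.1% |
| 0.5 | 15.7% | 20.7% |
| 0.7 | 12.9% | 16.4% |

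Between correlations of 0 and 0.5 this is roughly 3 to 5 times the nominal 5%.

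**Step 4. Parent and child scores alone.** With two independent tests at 5%, the chance of at least one false positive is 1 − 0.95² = 9.8%. Splitting the level for two tests gives 2.5% at the first Holm step. t-based power for each score at effect size 0.6:

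| Scores per arm | Two-sided 5% | Two-sided 2.5% |
|---|---|---|
| 45 | 80.4% | 71.4% |
| 50 | 84.4% | 76.4% |
| 54 (108 in total) | 87.1% | 79.9% |

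**The case against.** **A separate analysis plan may deal with multiplicity.** This is the strongest defence. A journal article condenses the full protocol, and adjustment rules are often left to the analysis plan, so the missing adjustment is not a fault on that ground alone. What remains is the contradiction: the article calls one outcome primary in one section and several in others, and a rule held elsewhere would still need to know which list it governs.

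**The trial is exploratory.** It is phase II, has a proof-of-concept aim, and the Discussion says further studies will be needed. This lowers the stakes of a false positive. It does not explain why four items carry the label primary beside a formal power calculation.

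**Sizing looked beyond satisfaction.** The sentence about the quiz shows that a second outcome was considered. It gives no inputs, is not described as a joint or adjusted calculation, and does not cover the questionnaire or diaries.

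Three stronger readings are tempting but unsupported:

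- That a chance primary success is likely. The computed risks are well below one half; it takes 14 independent tests at 5% to exceed 50%.
- That there are ten primary tests. This needs the four questionnaire sections tested separately and the quiz split by time point. The article describes the sections and time points, but does not say that each will be tested.
- That power falls short because parent and child scores must both be significant. The article contains no such requirement.

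**Conclusion.** The concern holds in a bounded form. The article contradicts itself on what is primary, does not identify the rater to whom the 80% power applies, and draws six comparisons from the primary list with no stated hierarchy.

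The sample size is right for one comparison. Read as any one success at 5%, the false-positive risk is about 16% to 21% at a correlation of 0.5, and 18.5% to 26.5% under independence, for four to six tests. These figures rest on that success rule, which the article neither states nor excludes, and on assumed correlations. Materially inflated is the fair description.

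**What to change.** Make these changes before the allocation code is broken. The Randomization and blinding section places that after data collection is complete, so there is time.

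1. Make satisfaction on the visual analogue scale the only primary outcome, as sized. Then either:
   - name the parent or the child score as primary, which keeps 80.4% power at 45 per arm; or
   - keep both and test them with Holm (smaller p-value at 2.5%, the other at 5% if the first is significant). State the power accordingly: for each score at the first step, 79.9% with 54 per arm, 76.4% with 50 and 71.4% with 45. The scale is completed straight after the intervention, so three-month dropout should matter little. The target is only approximately 108, however, and simple randomization does not guarantee 54 in each arm.
2. Make the quiz, dietary questionnaire and diaries secondary, reported with 95% confidence intervals and no confirmatory claim.
3. Bring the abstract, primary aim (ii), the Sample size section and the Outcome measures list into agreement. Leaving aim (ii) as it stands would create a new contradiction.

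**Cost:** no extra recruitment if a single score is named. Under Holm, power stays near 80% only with about 54 scores per arm. Knowledge and behaviour outcomes lose primary status and, because Trial status reports recruitment as ongoing, the change needs a documented amendment dated before unblinding.

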After the baseline measures are completed, AA will introduce the participants to the dental nurse and leave, to ensure that he remains blinded to group allocation. The nurse will then allocate the participants to either the video-game group or the control group according to the randomization grid and will apply the intervention accordingly.

The nurse will administer postintervention measures to both groups including: (i) pictorial dietary quiz, completed by the child; (ii) child’s and parent’s satisfaction with intervention on a visual analogue scale; (iii) a booklet that contains a toothbrushing diary and a snack diary, to be returned on the day of the general anaesthesia procedure. The booklet given to children from the study group will also contain a page in which they can write five ‘secret words’ that have been inserted in the DVD version of the game. This will allow us to determine whether participants used the game DVD at home. Children from the control group will have a simple colouring page instead. Finally, (iv) the nurse will ask the parent and child if they have any feedback on the intervention; this feedback will be written down verbatim (qualitative data).

AA will go to the day surgery unit on the day of the child’s general anaesthesia procedure to collect the booklet. He will also call the participating parents three months after their child’s general anaesthesia procedure and offer them a review appointment at the paediatric dentistry department. Upon attending, the parents of both groups will be asked to complete the children’s dietary questionnaire again, to measure any changes in dietary practices at home. The child will be asked to retake the pictorial dietary quiz to assess long-term retention of dietary knowledge. Attendance rates from both groups will be noted.

Fig. 2 is a summary of the recruitment process and the measures collected.

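### The recruitment target of 108 multiplies by 1.2 where it should divide by 0.8, so 20% loss leaves about 86 rather than 90, and the plan does not say which outcome the 20% protects

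*Protocol article*

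**What the plan says.** The Sample size section of the protocol article builds its calculation on satisfaction: "The primary outcome measure in this study is user satisfaction with the intervention, assessed using a visual analogue scale". The inputs are a spread ("Assuming that our population will have a standard deviation of 25 mm") and a target difference ("aiming to detect a difference of at least 15 mm between the groups"), which lead to "a sample of 45 participants in each group will be needed to provide 80 % power, at the 5 % significance level". The section adds that this number is also enough for the pictorial dietary quiz, on separate calculations from the phase-I trial that are not shown. It then anticipates 20% dropout and ends: "we intend to recruit approximately 108 participants".

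The abstract (Methods/Design) gives an upper limit: "Up to 110 four- to ten-year-old children, referred for tooth extraction under general anaesthesia due to caries, will be recruited".

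On timing, the Procedure section lists "child’s and parent’s satisfaction with intervention on a visual analogue scale" among the measures that the nurse gives after the intervention, at the same clinic visit as consent and baseline. The diaries come back on the day of the anaesthetic. The quiz and the dietary questionnaire are repeated at the 3-month review. The Outcome measures section lists all of these as primary.

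**The concern.** An allowance for dropout should leave the required number after the expected loss. Here it does not: the target falls short of the section's own 90 at the section's own 20%. A reader will reasonably take 108 as the number that keeps 45 per group at that rate.

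The allowance is also not tied to any outcome or time point. The outcome with a shown calculation is measured minutes after randomisation, so follow-up loss hardly touches it. The outcomes exposed to loss have no shown calculation. One recruitment figure therefore describes neither situation accurately: the precision of the satisfaction comparison is probably better than stated, and the number left at follow-up is lower than implied.

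**Working it through.** **Inputs.** From the Sample size section: SD 25 mm, difference 15 mm, power 80%, significance level 5%, 45 per group, dropout 20%, target 108. From the abstract: ceiling 110. Sidedness is not stated. Two-sided is assumed because it reproduces 45; a one-sided test would need 36 per group.

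**Step 1: the base size.** The standardised effect is 15/25 = 0.6.
- Normal approximation: n = 2 × (1.960 + 0.842)² / 0.6² = 43.6, so 44 per group.
- t test: 44.6, so 45 per group.

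The stated 45 per group, 90 in total, reproduces.

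**Step 2: the inflation.**
- Needed to retain 90 after 20% loss: 90 / (1 − 0.20) = 112.5, so 113 (114 with equal groups).
- Multiplying instead: 90 × 1.20 = 108, which is the stated target exactly.

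**Step 3: what the stated numbers retain.**
- 108 × 0.80 = 86.4, about 86, or 43 per group.
- 110 × 0.80 = 88, or 44 per group.
- Largest loss that still leaves 90: 1 − 90/108 = 16.7% with 108 recruited; 1 − 90/110 = 18.2% with 110.

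**Step 4: power for 15 mm on the satisfaction scale.** Two-sided 5% t test, equal groups, non-centrality 0.6 × √(n/2).

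| Per group | Situation | Power | Difference detectable with 80% power |
|---|---|---|---|
| 45 | as required | 80.4% | 14.9 mm |
| 43 | 108 recruited, 20% lost | 78.5% | 15.3 mm |
| 54 | 108 recruited, none lost | 87.1% | 13.6 mm |

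If the 20% applied to the satisfaction scale, the inflation error would cost 80.4 − 78.5 = 1.9 percentage points.

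**Step 5: which row applies.** The Procedure section puts the satisfaction scale at the randomisation visit, directly after the intervention. If few families leave before completing it, the 54-per-group row is the relevant one. Later loss affects diary return, the 3-month quiz and the 3-month dietary questionnaire. For those outcomes the documents give no effect size and no SD, so no power can be computed from them.

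**The case against.** The best defence is that the error does little harm. The target is given as approximate, the shortfall against 113 is five recruits, and the assumed SD is borrowed from other fields and is far less certain than a two-point change in power. If same-day loss is negligible, the only outcome with a shown calculation has more power than claimed. On the normal approximation, 44 per group already gives 80.4%, so 110 recruits less 20% would do; by t test, 44 gives 79.5%. All of this stands, and it limits the weight of the point. It does not make 108 the right inflation of 90: the figure matches the wrong formula exactly, and even the abstract's ceiling does not leave 90 after 20% loss.

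Three stronger readings are tempting, and the documents do not support them.
- **That the 3-month outcomes have about 78% power.** That figure carries the satisfaction effect of 0.6 SD and a two-group t test over to other measures. The quiz was sized on calculations that are not shown and is to be analysed by regression over three time points, so it may need fewer than 43 per group. No size target is given for the dietary questionnaire.
- **That a 3-month dropout rate was wrongly applied to a same-day outcome.** The section ties the 20% to no time point. The reference given for it is cited again in the Discussion as support for the visual analogue scale, so what the 20% represents cannot be settled from the text. The allowance is unassigned, which is different from misapplied.
- **That the abstract and the Sample size section contradict each other.** One gives a ceiling of 110 and the other a target near 108; both can be true.

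**Conclusion.** The point holds as a definite but small arithmetic error, together with an allowance whose purpose is not stated. The section says "a sample of 45 participants in each group will be needed", yet 108 recruits with 20% loss leave about 43 per group. The target delivers 45 per group only if loss is at most 16.7%.

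The trial cannot be called underpowered for satisfaction on this ground, since that scale is completed at the randomisation visit and probably keeps close to 54 per group. For the outcomes that do face follow-up loss, the documents show that about 86 would remain at 20% loss, but not what power that gives.

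These figures assume a two-sided test, the stated SD of 25 mm, and groups of equal size. Simple randomisation will not guarantee the last, but modest imbalance would change little.

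**What to change.** No extra recruitment is needed. Revise the end of the Sample size section so that it says:
- 108 recruited retains 45 per group only if loss does not exceed 16.7%;
- 20% loss would leave about 86 (43 per group), with about 78% power for 15 mm if that loss applied to the satisfaction scale;
- the satisfaction scale, completed at the intervention visit with negligible loss, has about 54 per group and about 87% power for 15 mm.

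State which outcome and time point the 20% refers to. Then check, with the phase-I calculation itself, whether 43 per group is still enough for the quiz, rather than assuming an effect of 0.6 SD. If it is not, say so.

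The abstract's ceiling of 110 can stay unless the sponsor chooses to raise the target to 113 or 114, in which case it must rise too.

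The cost is a few restated figures and one check of an existing calculation. Design and conduct do not change, so this can be done while recruitment continues.

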#### Randomization and blinding

A computer-generated simple randomization grid will allocate the participants to the two groups. The randomization process will be overseen by the unblinded researcher (MTH). The allocation of participants will be performed by the two trained dental nurses responsible for applying the interventions to the participants. The researcher (AA) will remain blinded all through data collection and input. The statistician will also be blinded during the analysis. Only after data collection is complete will one researcher (MTH) break the randomization code to input the group allocation within the pre-existing data set and enable between-group analyses. The statistician and lead researcher (AA) will remain blinded.

#### Procedure for recruitment and application of intervention

Each week, the blind researcher (AA) will obtain a list of all children attending the medical pre-assessment clinic for general anaesthesia for dental purposes. Those who are younger than four or older than ten will be excluded.

Next, AA will go through the clinical notes of the remaining children to determine their eligibility to participate. At this stage, children who are having treatment for dental conditions other than caries, or with medical conditions affecting dental health or learning difficulties, and those children participating in other studies can be identified and excluded. All children accompanied by parents or guardians that require an interpreter to provide consent for the general anaesthesia procedure will also be excluded. However, the total number of those children will be recorded. The research will also record the different languages of the non-English speakers. South London is a culturally and ethnically diverse area, and keeping records of the languages spoken by those children and their families will help assess the local area’s future need for versions of the video game in different languages.

On the day of the clinic, AA will approach all potential participants, invite them to take part, and explain the study to them. At this stage, children accompanied by adults who cannot provide consent for them (aunt or uncle, older sibling, *etc*.) and those who do not display enough English proficiency to take part will also be excluded. AA will aim to approach every potential participant matching the inclusion criteria; however, some potential participants will be missed, as they will arrive and leave their appointment while a participant is taking part in the study.

Parents who indicate their agreement to take part will be asked to provide written consent and their child will be asked for assent. AA will then administer three following baseline measures. A pictorial dietary quiz will be completed by the child. This is the same quiz used in the phase-I pilot. (ii) A children’s dietary questionnaire will be completed by the parent. This is a validated measure used to report the dietary habits of children aged 4–16 years [31]. It includes four sections (covering intake of fruit and vegetables, dairy, sweet drinks, and non-core foods). Finally, details of the child’s most recent snack at school will be provided by the child.

After the baseline measures are completed, AA will introduce the participants to the dental nurse and leave, to ensure that he remains blinded to group allocation. The nurse will then allocate the participants to either the video-game group or the control group according to the randomization grid and will apply the intervention accordingly.

The nurse will administer postintervention measures to both groups including: (i) pictorial dietary quiz, completed by the child; (ii) child’s and parent’s satisfaction with intervention on a visual analogue scale; (iii) a booklet that contains a toothbrushing diary and a snack diary, to be returned on the day of the general anaesthesia procedure. The booklet given to children from the study group will also contain a page in which they can write five ‘secret words’ that have been inserted in the DVD version of the game. This will allow us to determine whether participants used the game DVD at home. Children from the control group will have a simple colouring page instead. Finally, (iv) the nurse will ask the parent and child if they have any feedback on the intervention; this feedback will be written down verbatim (qualitative data).

AA will go to the day surgery unit on the day of the child’s general anaesthesia procedure to collect the booklet. He will also call the participating parents three months after their child’s general anaesthesia procedure and offer them a review appointment at the paediatric dentistry department. Upon attending, the parents of both groups will be asked to complete the children’s dietary questionnaire again, to measure any changes in dietary practices at home. The child will be asked to retake the pictorial dietary quiz to assess long-term retention of dietary knowledge. Attendance rates from both groups will be noted.

Fig. 2 is a summary of the recruitment process and the measures collected.

